## 8 STUDY PROCEDURES

### 8.1 Study Flow Chart/Table of Study Procedures and Assessments

This study consists of an online survey disseminated on November 7, 2022, (timepoint  $T_{-1}$ ), followed by an in-person visit taking place on November 8, 2022, during which either the active or control intervention will be administered (**Figure 1**).  $T_0$  specifies the pre-intervention period,  $T_1$  the post-intervention timepoint on the date of the in-person visit. Detailed decision guidelines are summarized in Figure 2.

In an introductory survey, study information will be provided and a number of characteristics will be recorded, such as the name, gender, year of birth, and previous experience with MT. In this same survey, the eligibility of the participants will be verified (**Table 1**).

On the day of the intervention, the intervention protocol, consisting of baseline measurement, application of active or control intervention, and outcome measurement will be performed. The process will take around ten minutes from  $T_0$  to  $T_1$ .

[figure not shown]

**Figure 1.** Study procedure of SENSATE: overview of the course of the trial.

[figure not shown]

**Figure 2.** SENSATE study flow.

## 8.2 Assessments of Outcomes

### Assessment of Primary Outcome – Blinding success in study participants

The primary outcome of the present study is blinding success in study participants. This will be measured using the Blinding Index according to Bang. The Blinding Index is derived from a five-point Likert scale inquiring about the degree of certainty regarding perceived intervention arm allocation in study participants (1 = “I strongly believe I received the active intervention”; 2 = “I somewhat believe I received the active intervention”; 3 = “I somewhat believe I received the control intervention”; 4 = “I strongly believe I received the control intervention”; and 5 = “I do not know”).

### Assessment of Secondary Outcomes

#### *Blinding success in study participants*

Blinding success in study participants will be measured with an alternative blinding index – James Blinding Index. Although this index requires different computational considerations, it can be derived from the previously described five-point scale inquiring about the degree of certainty regarding perceived intervention arm allocation (1 = “I strongly believe I received the active intervention”; 2 = “I somewhat believe I received the active intervention”; 3 = “I somewhat believe I received the control intervention”; 4 = “I strongly believe I received the control intervention”; and 5 = “I do not know”).

#### *Blinding success in outcome assessors*

The Blinding success in the outcome assessors will be measured using the Blinding Index according to Bang. The scale is the same as described for the primary outcome. The question will refer to the degree of confidence of the assessor that participants have received either the active or the control intervention (1 = “I strongly believe they received the active intervention”; 2 = “I somewhat believe they received the active intervention”; 3 = “I somewhat believe they received the control intervention”; 4 = “I strongly believe they received the control intervention”; and 5 = “I do not know”).

#### *Factors contributing to perceptions about intervention assigned*

Contributing factors to perceived intervention arm allocation will be assessed qualitatively. Participants and outcome assessors will be asked one open-ended question about the reason why they believe that they received/or administered the active or control intervention.

#### *Assessment of the different dimensions of low back function*

The low back function dimensions will be assessed using objective and self-reported subjective measures.

ROM assessment: Participant’s lumbar spine flexion–extension ROM both pre- and post-intervention will be measured using the pre-installed iOS application called *Measure*® (iOS version 16.0.2, iPhone® model X, Apple Inc., California) following the SOP in Appendix I. Mobile applications were suggested as valid and reliable tools to assess lumbar spine flexion–extension ROM. While standing, each participant will be asked to perform maximum spinal extension and flexion with extended knees. No instructions will be provided to participants regarding the velocity of movements. Thus, all participants will perform the movements at their preferred speed, which is known to produce more consistent results of motion characteristics, than pre-defined slow or maximum speed.

Self-reported back flexibility will be measured using an item from the validated International Fitness Scale (IFIS). Furthermore items from the Cornell Musculoskeletal Discomfort Questionnaire (CMDQ) will be used to assess current experience of pain, ache, or discomfort in the upper back as well as in the lower back, and their corresponding intensities.

## 8.3 Assessment of Safety Outcomes

### Serious Adverse Events

Serious adverse events (SAE) will be recorded as part of the outcome measurements. We do not anticipate any risks associated with participation in this study. In case participants experience adverse events, they will be asked to notify the principal study investigator as described in our informed consent form.

#### **Assessments in Participants who Prematurely Stop the Study**

Participants not complying with interventions or premature exclusion for other reasons are asked to participate in the outcome measurements at least partly (e.g., only questionnaire). If possible, the withdrawal reason is recorded. There will not be any follow-up visits or assessments.

### **8.4 Procedures at Each Visit**

#### **Intervention visit**

##### **Introduction**

- Oral information of study protocol
- Signing of informed consent
- Self-assessment of back flexibility of the patient via survey

##### **Baseline measurement**

- Measurement of ROM before intervention

##### **Intervention**

- Randomized allocation to active or control intervention
- Administration of active or control intervention (see SOP in Appendix I)

##### **Outcome measurement**

- Assessment of blinding (questionnaire)
- Measurement of ROM after intervention

## **9 SAFETY**

During the entire duration of the study, all serious adverse events (SAEs) actively reported by the participant in relation to the study intervention are collected and documented in source documents in the case report form (CRF). Study duration encompasses the time from when the participant signs the informed consent until the last protocol-specific procedure has been completed.

### **9.1 Definitions**

#### **Adverse events**

Adverse events (AEs) are defined as any untoward medical occurrence in a clinical investigation participant after the intervention. An AE can therefore be any unfavorable and unintended sign (including an abnormal laboratory finding), symptom, or disease temporally associated with the intervention, whether or not related to the intervention. It may also consist of a new disease, an exacerbation of a pre-existing illness or condition, a recurrence of an intermittent illness or condition, a set of related signs or symptoms, or a single sign or symptom.

#### **Serious Adverse Event**

A serious adverse event is defined as any event which:

- requires inpatient treatment not envisaged in the protocol or extends a current hospital stay
- results in permanent or significant incapacity or disability

- is life-threatening or results in death or
- causes a congenital anomaly or birth defect.

## 9.2 Recording and Assessment of Serious Adverse Events

The investigator has the responsibility for SAE identification, documentation, and assessing the causal relationship study intervention. Participants are instructed to actively report any SAE to the study PI.

All reported SAEs will be fully documented in the appropriate *eCRF*. For each SAE, the investigator will provide the onset, duration, treatment required, outcome and action taken with regard to the study intervention.

The assessment by the investigator with regard to the study intervention relation is done according to the following definitions:

|                  |                                                                                                                                                                                                                                                    |
|------------------|----------------------------------------------------------------------------------------------------------------------------------------------------------------------------------------------------------------------------------------------------|
| Unrelated | 
 
• The event started in no temporal relationship to the medical intervention applied and
 
• The event can be definitely explained by underlying diseases or other situations.
 
             |
| Related   | 
 
• The event started in a plausible temporal relationship to the medical intervention applied and
 
• The event cannot be definitely explained by underlying diseases or other situations.
 
 |

## 9.3 Reporting of Serious Adverse Events

If, in the course of a clinical trial, serious adverse events occur in participants in Switzerland, and it cannot be excluded that the events are attributable to the intervention under investigation, the investigator must report these events:

- to the sponsor **within 24 hours** after they become known; and
- to the CEC **within 15 days**.

### Safety and protective measures

If immediate safety and protective measures have to be taken during the conduct of this clinical trial, the investigator must notify the CEC of these measures, and of the circumstances necessitating them, **within 7 days**.

## 10 STATISTICAL METHODS

To assess blinding success within our study, we will use the blinding index (BI) as proposed by Bang et al. and James et al. They will be used to assess blinding success of both participants (Bang and James) and outcome assessors (Bang only).

### 10.1 Sample Size Consideration

A precision-based approach has been used to consider sample size (i.e., width of the 95% CI) for the Bang BI estimates rather than statistical power given this is a methodological feasibility randomised trial. We propose to estimate the Bang BI for each group and present a 95% CI for each mean BI point estimate. For a sample size of 26 participants in total (the maximum given our limited class size), the 95% CI will be the observed BI estimate  $\pm 0.315$  points (0.63 points width of the 95% CI) for the primary outcome measure of the group-specific Bang BI, according to Thompson's method (Eq 1) as described by Landsman and colleagues in their study on sample size calculations for blinding assessments. The small class size will inherently limit the precision of our

estimated BI. Ideally, we would want to carry out this trial in a larger study population of approximately 40 participants (20 per group) for a 0.50 points width of the Bang BI 95% CI.

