### 5 STUDY DESIGN AND COURSE OF STUDY

#### 5.1 General Study Design and Justification of the Design

This feasibility trial is a two-arm parallel randomized controlled trial (1:1 allocation ratio) that compares an active and control intervention in terms of blinding success. Based on pre-piloting, enrolled participants will be able to complete outcome assessments and interventions in approximately ten minutes. Individual participants will be assigned a specific time slot during the day of the trial execution. An initial intake form will be filled out by study participants via Research Electronic Data Capture (REDCap 12.5.14) the day before the clinical trial is conducted.

The two tested interventions target the back region and pose minimal risks, even for asymptomatic populations. The active intervention will be operationalized as passive soft tissue mobilization of the lumbar paraspinal muscles with the patient laying in a prone position. The control intervention will be operationalized as a series of bilateral light touches that follow the rhythm of deep breathing of the participant applied at the level of the scapular region and more caudally to the level of the lower part of the rib cage (T12). The control intervention is not known to have any beneficial effects and closely resembles a validated MT sham proposed, thus providing reasonable structural equivalence with respect to the active intervention.

The study population will be restricted to a convenience sample of graduate students from the University of Zurich. There is limited preliminary information regarding the sociodemographic characteristics of this study population and how it may relate to the general graduate student population of Switzerland. It is also unclear how the underlying characteristics of this student population may influence our blinding assessment.

To ensure blinding of participants, outcome assessors and data analysts, the study will be conducted in two different rooms at the University of Zurich. In addition, two different REDCap accounts will be created to prevent accidental unblinding of outcome assessors and data analysts within the REDCap system.

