### **6.2 Recruitment and Screening**

All students enrolled in the “EPI301 Introduction to Epidemiology” course are eligible for participation. Participant eligibility will be determined based on the self-disclosure regarding potential exclusion criteria determined on the day of the study. Study participants will incur no charge upon enrollment into the study nor receive any financial reward for participation.

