### Primary Analysis

Blinding indices  $BI_i$  and their respective 95% confidence intervals as defined by Bang et al. will be calculated for each study arm  $i = 1$  for active and  $i = 2$  for sham

$$BI_i = \frac{(2\bar{r}_{i,i} - 1) \cdot (n_{i1} + n_{i2})}{(n_{i1} + n_{i2} + n_{i3})}$$

The Bang index ranges from  $-1$  (opposite guessing related to unblinding) to  $1$  (complete lack of blinding), and can be interpreted as the proportion of participants who guess the intervention correctly over incorrect guesses, including the “don’t know” answer category. In the above formula,  $\bar{r}_{i,i}$  denotes the proportion of correct guesses across the whole population. Successful blinding in the Blinding Index by Bang et al. was predefined as a value from  $-0.2$  to  $0.2$  in the blinding index point estimate. This range will also eventually be used in our analysis as evidence of successful blinding.

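### The single 95% CI margin given for the group-specific Bang index (±0.315 at 26 in total, width 0.50 at 20 per group) is too narrow for the printed index unless about two thirds answer don't know

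*Protocol*

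**What the plan says.** Section 10.1 justifies the sample size by precision rather than power. It starts from the class ceiling, "For a sample size of 26 participants in total (the maximum given our limited class size", and plans to "present a 95% CI for each mean BI point estimate". It then fixes the margin at ±0.315, "0.63 points width of the 95% CI) for the primary outcome measure of the group-specific Bang BI", obtained "according to Thompson's method (Eq 1" of a cited sample-size paper. It adds that the authors would ideally have "approximately 40 participants (20 per group) for a 0.50 points width of the Bang BI 95% CI". No expected index value and no expected share of don't-know answers goes with either figure.

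Section 5.1 describes a "two-arm parallel randomized controlled trial (1:1 allocation ratio", so 26 in total means 13 per arm. Under Primary Analysis in section 10.2, the index and its 95% interval, in the form defined by the index's authors, "will be calculated for each study arm". The formula there has three response categories (two guesses and don't know), and the index runs from −1 to 1. Blinding counts as successful if the point estimate lies between −0.2 and 0.2. Section 8.2 collects answers on five options, and Secondary Analyses says both indices will be calculated from those five-option answers. No weights for the two levels of certainty are given.

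**The concern.** The Bang index is a difference between two proportions from the same arm. A person who guesses correctly cannot also guess incorrectly, so the two proportions are negatively correlated and their difference varies more than either one alone. Its interval also depends on how many people decline to guess. One fixed margin, with no don't-know share attached, therefore cannot be the interval of this index in general, and ±0.315 looked small for 13 people.

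The margin is the protocol's only quantitative planning statement for its primary outcome. If it is too small, readers will expect more from the trial than it can give. The figure of 20 per group for a width of 0.50 could also mislead anyone who plans a later blinding study from this one.

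**Working it through.** **Inputs.** From the protocol: 26 in total at 1:1, hence n = 13 per arm; 95% confidence; stated half-width 0.315 at 13 per arm; stated width 0.50 (half-width 0.25) at 20 per arm; the three-category formula under Primary Analysis. Assumed, because the protocol gives no values: true index near 0, and a don't-know share q from 0 to one third, with higher shares as sensitivity cases. In the formula, r is read as the share correct among those in the arm who guess.

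**1. Reproducing the stated figures.** The cited paper is not at hand, so this uses the standard Thompson rule for multinomial samples. That rule makes every category proportion lie within ±d simultaneously: n = max over m of z(1 − 0.05/(2m))² × (1/m)(1 − 1/m) / d². The maximum is at m = 3 and gives n × d² = 1.2736.

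- n = 13: d = √(1.2736/13) = 0.313. Conversely, d = 0.315 needs n = 12.8.
- n = 20: d = √(1.2736/20) = 0.252. Conversely, d = 0.25 needs n = 20.4.

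Both stated pairs match. An ordinary 95% margin for one proportion at n = 13 does not: it is 0.272 at p = 0.5. A second route also comes close. The Bang margin with total n instead of arm n, one third don't know and an index of 0 gives 1.96 × √((2/3)/26) = 0.314 and 1.96 × √((2/3)/40) = 0.253.

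**2. Variance of the printed index.** With r = n_correct/(n_correct + n_incorrect), the formula becomes (n_correct − n_incorrect)/n, that is p_correct − p_incorrect. Its multinomial variance is [p_correct + p_incorrect − (p_correct − p_incorrect)²]/n. At an index of 0 the 95% half-width is 1.96 × √((1 − q)/n).

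| Don't-know share q | Half-width, n = 13 | Ratio to 0.315 | Half-width, n = 20 | Full width, n = 20 |
|---|---|---|---|---|
| 0 | 0.544 | 1.73 | 0.438 | 0.88 |
| 20% | 0.486 | 1.54 | 0.392 | 0.78 |
| one third | 0.444 | 1.41 | 0.358 | 0.72 |
| half | 0.384 | 1.22 | 0.310 | 0.62 |
| two thirds | 0.314 | 1.00 | 0.253 | 0.51 |

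Setting 1.96 × √((1 − q)/13) = 0.315 gives q = 0.664.

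**3. Size needed for the stated widths.** n = 1.96² × (1 − q)/d². For d = 0.25 this gives 62 per arm (q = 0), 41 (one third) and 31 (half). For d = 0.315 it gives 39, 26 and 20.

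**4. Index away from 0.** At n = 13 and one third don't know, an index of 0.2 gives 0.430 and an index of 0.5 gives 0.351 (11% above 0.315). With half don't know and an index of 0.5 it is 0.272, which is below 0.315.

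**5. Five-level version (assumed weights 1 and 0.5).** At n = 13 and an index of 0, with everyone guessing, the half-width runs from 0.272 (all less certain) through 0.430 (four guesses used equally) to 0.544 (all certain). With all five answers used equally it is 0.384.

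**6. Coverage.** In simulation at n = 13 and true index 0 (three categories), an interval of ±0.315 covers about 87% with one third don't know and about 73% with none.

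**The case against.** Several points on the other side carry weight.

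*The source of the figure is not proved.* A reader might infer that the protocol took a margin for category proportions and labelled it as the margin of the index. The match at both sample sizes makes that likely, but the cited equation cannot be checked here, and the total-n route also nearly matches. This limits what can be said about the cause. It does not rescue the figure: the total-n route is also wrong for a group-specific index, since with equal arms it understates the margin by a factor of √2.

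*The shortfall is not a fixed percentage.* A reader might infer that the true interval is always 40 to 70% wider. That holds for the three-category index near 0 with don't-know shares from one third down to none. It shrinks or disappears with many don't-know answers, or when the index is far from 0. Under five-level weighting, 0.315 lies inside the possible range. This stands, and the conclusion has to be conditional. The protocol, however, states none of these favourable conditions and gives a single figure as what the interval will be.

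*Nothing is decided by the margin.* Class size fixes enrolment, success is judged on the point estimate, and each arm's index will be reported with its own calculated interval. Section 10.1 already admits that the class size limits precision. This stands and lowers the severity. A reader might go further and infer that the success rule is invalidated. It is not: the stated width of 0.63 already exceeds the 0.40 span of the success range, so the correction changes nothing there.

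*Non-participation.* A reader might add that the figure wrongly assumes the whole class takes part. Section 10.1 calls 26 the maximum, so this is not an error in the text.

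**Conclusion.** Wrong as written, and it should be fixed. For the three-category index that the protocol prints, with an index near 0, the 95% half-width at 13 per arm is about 0.44 to 0.54 (one third to no don't-know answers) and 0.38 with half. It equals the stated 0.315 only at about 66% don't know. At 20 per arm the full width is about 0.72 to 0.88, not 0.50, and a width of 0.50 needs about 41 to 62 per arm.

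This rests on the multinomial variance of the printed index with a normal-approximation interval, and on assumed don't-know shares. It does not depend on how the stated figures were derived. If a weighted five-level index is intended, the half-width at 13 per arm could be 0.27 to 0.54 on the assumed weights, and the protocol would need to state the weights before any margin can be quoted. The documents do not support reading this as a reason to change enrolment or to discard the analysis.

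**What to change.** In section 10.1, replace both precision statements with half-widths computed from the variance of the index that will be reported. State the assumed index value, the don't-know share and any weights. For the three-category index, suitable text would be: assuming a Bang index of 0 and between one third and no don't-know answers, the 95% CI half-width is expected to be about 0.44 to 0.54 with 13 per arm and about 0.36 to 0.44 with 20 per arm. Correct the aspiration of 20 per group for a width of 0.50 accordingly: under the same assumptions it is about 41 to 62 per arm. If Thompson's method is kept as a citation, check the cited equation and say which quantity its margin applies to.

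The cost is one paragraph. The stated precision becomes less favourable; enrolment, randomization and the planned analysis stay as they are.

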## 10.2 Planned Analyses

Statistical analysis will be performed with R.

### Datasets to be Analyzed, Analysis Populations

The analysis population will consist of all participants included in the study as assigned to the respective intervention, following an intention-to-treat approach. Data analysis will be performed by masking (i.e., pseudonymizing) the intervention arm allocation (active or control) of participant data.

### Primary Analysis

Blinding indices  $BI_i$  and their respective 95% confidence intervals as defined by Bang et al. will be calculated for each study arm  $i = 1$  for active and  $i = 2$  for sham

$$BI_i = \frac{(2\bar{r}_{i,i} - 1) \cdot (n_{i1} + n_{i2})}{(n_{i1} + n_{i2} + n_{i3})}$$

The Bang index ranges from  $-1$  (opposite guessing related to unblinding) to  $1$  (complete lack of blinding), and can be interpreted as the proportion of participants who guess the intervention correctly over incorrect guesses, including the “don’t know” answer category. In the above formula,  $\bar{r}_{i,i}$  denotes the proportion of correct guesses across the whole population. Successful blinding in the Blinding Index by Bang et al. was predefined as a value from  $-0.2$  to  $0.2$  in the blinding index point estimate. This range will also eventually be used in our analysis as evidence of successful blinding.

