### Secondary Analyses

For our secondary analyses, we will quantitatively evaluate participant’s blinding with James’s BI. The range of this complementary index ranges from  $0$  (all correct) to  $1$  (all incorrect) and does not provide different values according to intervention. An index of  $0.5$  (half correct, half incorrect) indicates random guessing. In addition, we will also assess blinding index in the outcome assessors using Bang’s BI after completing and documenting measurements at  $T_1$ .

Both blinding indices (Bang and James) will be calculated with the R package {BI} based on the participant responses about their degree of confidence in their assigned intervention group (displayed in 5-point Likert scale format).

In the secondary analysis, the measured change in ROM (maximum flexion and extension) of the thoracolumbar spine will be compared within and between the intervention groups (active vs. control;  $T_0$  vs.  $T_1$ ), although formal statistical testing of difference between groups will not be performed, as this would not align with our primary objective. In case a large difference in baseline characteristics is detected between the groups, regression analysis with adjustment of anticipated confounders (i.e., age, gender, experience with MT, care-seeking history for LBP) may be considered.

Contributing factors to perceived intervention arm allocation in study participants, as well as outcome assessors, will be qualitatively analyzed using thematic analysis. Two study investigators will collate collected responses, group them thematically and develop emerging clusters using a consensus-based approach.

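### The primary Bang index is computed for each arm, but its key term r is described as a proportion over the whole population

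*Protocol*

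**What the plan says.** Under Primary Analysis (section 10.2), the indices and their 95% confidence intervals "will be calculated for each study arm", with i = 1 for active and i = 2 for sham. The formula is BI_i = (2r_ii − 1)(n_i1 + n_i2)/(n_i1 + n_i2 + n_i3). The text then states that r_ii "denotes the proportion of correct guesses across the whole population". The three counts are not defined. The index is said to run from −1 to 1, with 1 meaning complete lack of blinding. Success is a value from −0.2 to 0.2 "in the blinding index point estimate".

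Section 10.1 gives the planned precision "for the primary outcome measure of the group-specific Bang BI, according to Thompson's method (Eq 1", so the intended quantity belongs to one arm. Secondary Analyses describes the James index, by contrast, as one that "does not provide different values according to intervention".

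On the input, section 8.2 says: "The Blinding Index is derived from a five-point Likert scale". The categories are strongly or somewhat active, somewhat or strongly control, and don't know. Secondary Analyses says that an R package will compute both indices "based on the participant responses about their degree of confidence in their assigned intervention group (displayed in 5-point Likert scale format".

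**The concern.** The definition of r and the rest of the primary analysis cannot both hold. A proportion taken over everyone in the trial is the same number for both arms, so it cannot carry what is specific to arm i. This is the primary outcome, and success is judged on the point estimate alone, so nothing else in the rule would catch a wrong r.

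The pattern most affected is the one where most participants in both arms believe that they received the active treatment. The active arm is then mostly right and the sham arm mostly wrong. A pooled r lets these cancel.

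A smaller matter is that the formula uses three counts while the responses have five categories, and no sentence links them.

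**Working it through.** **Inputs.** 26 participants in total (section 10.1) and 1:1 allocation (section 5.1), so 13 per arm. The formula and the ±0.2 limits are from Primary Analysis. Assumption: n_i1, n_i2 and n_i3 are the numbers in arm i guessing active, guessing control and answering don't know. Below, c, w and d are the numbers correct, wrong and don't know in an arm, so c + w = n_i1 + n_i2.

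**The plan's own figure.** The protocol gives no worked value of the index. Its one figure for the group-specific index is a half-width of 0.315. Thompson's worst-case multinomial rule has the constant 1.2736 (reached at m = 3), so the half-width is √(1.2736/13) = 0.313 with 13 participants and √(1.2736/26) = 0.221 with 26. The printed figure fits 13, which confirms that the intended unit is one arm. I use it only for that.

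**What r must be.** Put r = c/(c + w), within arm i:

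(2c/(c + w) − 1)(c + w)/(c + w + d) = (c − w)/n_i.

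This agrees with the stated range: an arm in which everyone guesses correctly scores 1. The multiplier (n_i1 + n_i2) cancels only if r's denominator is the same set of people, those in arm i who named an arm.

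**Reading A: r pooled over both arms, among those who named an arm.** Then BI_i = (2r − 1) × (share of arm i naming an arm). The second factor is never negative, so both arms must have the same sign or both be zero. With no don't-know answers the two indices are identical.

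| Active c/w/d | Sham c/w/d | Within-arm BI (active, sham) | Pooled r | BI as written (active, sham) |
|---|---|---|---|---|
| 13/0/0 | 0/13/0 | +1, −1 | 13/26 = 0.50 | 0, 0 |
| 10/3/0 | 3/10/0 | 7/13 = +0.54, −7/13 = −0.54 | 13/26 = 0.50 | 0, 0 |
| 9/2/2 | 3/8/2 | 7/13 = +0.54, −5/13 = −0.38 | 12/22 = 0.545 | (0.0909)(11/13) = +0.08 in each |

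In all three rows both arms fail the ±0.2 rule on the within-arm index and pass it as written. The first row is the limiting case: everyone says active, and an arm with complete lack of blinding scores 0.

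**Reading B: r over all 26, don't-know answers included.** Take 4/4/5 in both arms. Then r = 8/26 = 0.308 and BI = (0.615 − 1)(8/13) = −0.24 in each arm. The within-arm value is (4 − 4)/13 = 0. Balanced guessing is declared unsuccessful, because don't-know answers are counted against the arm twice.

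**Three counts and five categories.** Adding responses 1+2 and 3+4 and keeping 5 apart gives the printed formula its three counts. A certainty-weighted index is a different number. Take an arm with 2 strongly correct, 5 somewhat correct, 3 somewhat wrong, 1 strongly wrong and 2 don't know. Collapsed, it scores (7 − 4)/13 = 0.23. With somewhat weighted 0.5 it scores (2 − 1 + 0.5 × (5 − 3))/13 = 0.15. The weight is my assumption, as the protocol gives none. At 0.25 and 0.75 the values are 0.12 and 0.19.

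**The case against.** The best defence is that one sentence is wrong and several nearby statements are right. The protocol says that the index follows its published definition, computes it for each arm, puts arm subscripts on r and on every count, and names a package for the calculation. Nobody is told to compute a pooled r by hand. If the package is run by arm as the index is defined at source, the sentence about r has no numerical effect. That stands, and it limits the likely harm. It does not make the sentence correct: the protocol would then describe an analysis that was not done, and anyone checking the result against it could get other numbers.

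A reader might infer that the success verdict would often be reversed. Nothing in the documents supports a frequency. Under Reading A, the verdict in at least one arm differs in 5,716 of the 11,024 possible pairs of arm tables at 13 per arm (52%). That count gives every table equal weight, so it is a share of tables and not a probability.

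A reader might also rank the five-category question with the error in r. The printed formula already implies the collapse, any weights are assumed, and a recoding rule can be left to an analysis plan. It is a request for clarification.

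**Conclusion.** The definition of r is wrong as written. It contradicts the per-arm calculation and subscripts in the same section and the group-specific measure in section 10.1. Followed literally, it can turn +0.54 and −0.54 into 0 and 0 and so reverse the success verdict in both arms, and it prevents opposite signs from appearing in the two arms. With don't-know answers in the denominator it can also fail a balanced pair of arms, at −0.24 instead of 0.

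These sizes rest on 13 per arm, on the assumed meaning of the three counts, and on chosen example tables. They show what the written rule does, not what the trial will observe. It would go too far to say that the primary result will be wrong, because the named package and the cited definition offer a correct route.

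**What to change.** In Primary Analysis, replace the sentence on r with: r_ii = n_ii/(n_i1 + n_i2), the proportion of correct guesses among participants of arm i who named an arm. Define n_i1, n_i2 and n_i3 as the numbers in arm i guessing active, guessing control and answering don't know.

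As a minor clarification, state that the printed formula uses responses 1+2, 3+4 and 5 as its three counts. If a weighted five-category index is intended, print that formula and its weights instead. The choice belongs to the authors, but it should be fixed before the allocation is linked to the responses. The same sentence can cover the outcome assessors' index, which uses the same scale.

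The cost is a few sentences in section 10.2. No data collection, sample size or software changes.
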